**Background**

The prevalence of overweight and obesity among children and adolescents has increased over the last two decades and has become a major public health problem [1,2]. According to the results of the German Health Interview and Examination Survey for Children and Adolescents (KiGGS), 15% of children and adolescents in Germany are overweight and 6.3% are obese [3]. Current treatment methods to reduce obesity and to mitigate complications such as insulin resistance and dyslipidemia are not considered to be successful [4], which emphasizes the importance of the development of obesity prevention concepts.

Evidence for new approaches for primary prevention has emerged from epidemiological and animal studies, suggesting that certain environmental factors during early childhood and the maternal milieu *in utero* during fetal development may have long-term consequences for human health throughout the life span. A multitude of studies have found relationships between fetal development and later risk for diseases such as diabetes or cardiovascular problems in adulthood [5-10]. In addition, there is evidence for an association between the development of overweight/obesity and metabolic influences on fetal development via poorly defined mechanisms called "fetal programming" [11,12]. Scientific data suggest that an increased pre-pregnancy maternal body mass index (BMI) is a risk factor for later childhood overweight. Additionally, gestational diabetes mellitus (GDM), which occurs more often in obese pregnant women, increases the child’s risk of becoming overweight and developing diabetes later in life. Recent data also suggest a potential “programming” effect of maternal weight gain during pregnancy on the fetal metabolic environment. Moreover, maternal obesity and GDM place the mother at a higher risk for adverse health outcomes such as type 2 diabetes or metabolic syndrome (abdominal obesity, elevated triglyceride levels, decreased HDL cholesterol levels, increased blood pressure, elevated fasting glucose levels) [13].

A number of biomarkers are already established for the biochemical characterization of overt obesity [14]. However, these do not permit any or only very limited conclusions regarding obesity risk. Such new "risk" biomarkers (e.g. metabolites) are currently not available but are essential for the safe management of early-onset nutritional prevention strategies in future clinical trials. In the prospective mother-child cohort study PEACHES, biomarker candidates for the early detection of obesity risk will be evaluated in "high-risk" newborns of obese mothers, who will have longitudinal follow-up throughout early childhood until the age of 5 years. Further, as a subproject of the PEACHES study, mothers with an increased “gestational risk profile” such as obesity will be evaluated for cardiometabolic dysfunction several years postpartum.

**Hypotheses and Aims**

Hypotheses:

1. Overt obesity is defined by systemic-metabolic dysregulation in the intermediary metabolism.
2. The effects of metabolic dysregulation before and/or during pregnancy are associated with the risk of subsequent overweight/obesity in the child.
3. The metabolic dysregulation that is associated with the risk of offspring overweight/obesity cannot be detected clinically at birth or in early life.
4. Changes in biomarker profiles in the child’s cells represent this systemic dysregulation of the intermediary metabolism at birth or in early life as an indicator for the risk of obesity.

Aim:
The aim is to derive early prognostic biomarker(s) for childhood obesity risk.

**Study population**

PEACHES is a prospective cohort study with two different study groups and two control groups. Study group 1 consists of obese women (pre-pregnancy BMI ≥ 30 kg/m²) without GDM and study group 2 consists of obese women with GDM. Accordingly, control group 1 consists of normal weight women (pre-pregnancy BMI ≥ 18.5 ≤ 24.9 kg/m²) without GDM, while control group 2 consists of normal weight women with GDM.

**Sample size**

The sample size for the PEACHES study was calculated by [name]. [name], Institute for Medical Information Processing, Biometry, and Epidemiology (IBE), Faculty of Medicine, Ludwig-Maximilians-Universität München, Munich, Germany.

Assumptions for the calculation:

- The prevalence of obesity in pre-school children of obese mothers (BMI at conception ≥ 30 kg/m^2^) is 23% [15,16].
- The odds ratio for the offspring to be obese (versus not obese) is 3. This strong effect was based on previous findings from various studies.
- The significance level was set at 5% and the power at 80%.

Assuming that 20% of children of obese mothers with a dysregulated biomarker profile and 20% of children of obese mothers with a non-dysregulated biomarker profile are at risk of developing obesity, *n*=184 obese pregnant women should be included in the study. Assuming that 40% of children of obese mothers with a dysregulated biomarker profile and 15% of children of obese mothers with a non-dysregulated biomarker profile are at risk of developing obesity, *n*=157 obese women should be included in the study. Assuming a 30 to 40% drop-out rate up to the examination time point at age 5 years, 300 obese pregnant women (study group 1) should be recruited. In addition, 30 normal weight healthy controls (control group 1) will also be recruited. This will facilitate the assessment of the prenatal influence of maternal obesity on a possible dysregulation of the biomarker panel at birth.

For the calculation of the study group of obese mothers with GDM, the same assumptions are made. It is therefore necessary to recruit an additional 300 obese mothers with GDM (study group 2) and 30 normal weight women with GDM (control group 2).

**Examination schedule**

Children will be examined at birth, at 3 to 4 months and 5 years of age. A study questionnaire will be mailed to the families 6 to 8 weeks after birth and then annually thereafter until age 5 years. Mothers will be examined 3 years postpartum.

**Variables**

**Exposure variables.** Maternal pre-pregnancy obesity, GDM status, and metabolic risk markers such as maternal HbA_1c_ at delivery and offspring metabolites in cord blood.

**Outcome variables.** Offspring outcomes at birth: Birth weight, large-for-gestational-age (LGA) birth weight, cord-blood C-peptide concentration.

Offspring longitudinal weight status: Offspring age- and sex-specific BMI *z*-score at follow-up visits and well-child visits, as well as waist circumference at 5 years.

Maternal postpartum follow-up: Development of prediabetic/diabetic conditions based on maternal HbA_1c_ and glucose concentrations following an oral glucose tolerance test, body weight, height, fat mass, waist and hip circumferences, blood pressure, intima media thickness, pulse wave analysis, and genetic markers.

**Other variables.** Other maternal and child information that is collected includes socioeconomic status, maternal health and risk factors during pregnancy (such as smoking, pregnancy weight gain, hypertension), maternal health behaviors postpartum, breastfeeding, and the child’s health behaviors including nutritional status.

**Statistical analysis**

- Descriptive analysis of baseline characteristics relating to maternal and offspring factors will be conducted using Student’s *t* test for continuous and chi-square test for categorical variables.
- Univariable and multivariable linear and logistic regression models will be used to estimate the associations between risk markers and continuous and categorical outcomes such as BMI, LGA birth weights, childhood overweight, and maternal prediabetic/diabetic conditions postpartum.
- Multivariable logistic regression models will be used to predict the categorical outcomes from candidate markers such as maternal HbA_1c_ at delivery; variable selection will be done using shrinkage methods. Diagnostic properties of the models for the prediction of the outcomes from candidate markers and other variables will be assessed using receiver operating characteristic (ROC) analysis with k-fold cross validation.

All analyses will be conducted in the statistical software package R.

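### Minor: Student's t test is named although obese and normal-weight women are compared at 300 to 30, where its error rate depends on equal spread; Welch's test does not and costs little

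*Protocol*

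**What the plan says.** The first item of the Protocol's Statistical analysis section covers "Descriptive analysis of baseline characteristics relating to maternal and offspring factors", which "will be conducted using Student’s *t* test for continuous and chi-square test for categorical variables". It does not say which groups are compared or whether variances are pooled.

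The second item concerns outcomes: "Univariable and multivariable linear and logistic regression models will be used to estimate the associations between risk markers and continuous and categorical outcomes". The Variables section lists maternal pre-pregnancy obesity among the exposures, and birth weight and cord-blood C-peptide among the outcomes. The third item uses logistic regression with shrinkage for prediction. All analyses are to be run in R.

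The Sample size section states that "300 obese pregnant women (study group 1) should be recruited" and that "30 normal weight healthy controls (control group 1) will also be recruited". It plans the same 300 and 30 for women with GDM. Of the healthy controls it says "This will facilitate the assessment of the prenatal influence of maternal obesity on a possible dysregulation of the biomarker panel at birth".

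**The concern.** Student's t test assumes equal variances. When the groups are of similar size, a breach of that assumption does little harm. At 10:1 it does not average out: the 300 set the pooled variance and the 30 set most of the real sampling error. If the obese group is the more variable one, the test becomes conservative and differences are missed. If the controls are, it rejects too often.

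Unequal spread is plausible here. Normal-weight women are confined to a BMI window of 24.9 − 18.5 = 6.4 units, whereas the obese groups have no upper limit. For BMI itself the SD in controls cannot exceed half the window, 3.2.

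The issue also reaches beyond the baseline table. An ordinary univariable linear regression of a continuous outcome on a two-group indicator gives the same statistic and p-value as the pooled t test. If birth weight or C-peptide is regressed on obese versus normal-weight status with ordinary standard errors, the distortion carries over.

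**Working it through.** **Inputs from the Protocol.** n₁ = 300 obese and n₂ = 30 normal-weight women per GDM stratum; significance level 5%, taken as two-sided. Pooling the strata gives 600 versus 60, still 10:1.

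**Input that is assumed.** The SD ratio. The Protocol gives no SDs, so a range is shown in both directions.

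**The plan's own figure.** The Protocol states no error rate or power for the t test. Its sample sizes of 184 and 157 come from a different calculation, a Wald test of the log odds ratio: N = (1.96 + 0.842)² × [1/(s·p₁(1−p₁)) + 1/((1−s)·p₀(1−p₀))] / (ln 3)². Here s is read as the share with a dysregulated profile and p₀ as the obesity risk among the others.

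- s = 0.20, p₀ = 0.20, p₁ = 0.4286: 183.6, rounded up to 184.
- s = 0.40, p₀ = 0.15, p₁ = 0.3462: 156.8, rounded up to 157.

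No t test enters, so the recruitment targets do not depend on this point.

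**Closed-form check of Student's test.**

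- Pooled variance: s² = [299·σ₁² + 29·σ₂²] / 328
- SE² that the test assumes: s² × (1/300 + 1/30)
- True SE²: σ₁²/300 + σ₂²/30
- k = assumed SE² / true SE²; level ≈ 2 × [1 − Φ(1.96·√k)]

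Example, obese:control SD 1.5:1. s² = (299 × 2.25 + 29) / 328 = 2.140. Assumed SE² = 2.140 × 0.03667 = 0.0784. True SE² = 2.25/300 + 1/30 = 0.0408. So k = 1.92, the effective critical value is 1.96 × 1.386 = 2.72, and the level is about 0.7%.

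The simulated column uses normal data with 200,000 runs per setting.

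| SD obese : control | s² | assumed SE² | true SE² | k | Student, closed form | Student, simulated |
|---|---|---|---|---|---|---|
| 1 : 1 | 1.000 | 0.0367 | 0.0367 | 1.00 | 5.0% | 5.0% |
| 1.25 : 1 | 1.513 | 0.0555 | 0.0385 | 1.44 | 1.9% | 1.9% |
| 1.5 : 1 | 2.140 | 0.0784 | 0.0408 | 1.92 | 0.7% | 0.7% |
| 2 : 1 | 3.735 | 0.1369 | 0.0467 | 2.93 | 0.1% | 0.1% |
| 1 : 1.25 | 1.050 | 0.0385 | 0.0554 | 0.69 | 10.2% | 10.3% |
| 1 : 1.5 | 1.110 | 0.0407 | 0.0783 | 0.52 | 15.8% | 15.7% |
| 1 : 2 | 1.265 | 0.0464 | 0.1367 | 0.34 | 25.3% | 25.3% |

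Welch's test simulates at 5.0 to 5.1% in every row.

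**Power.** For a true difference of 0.55 control SDs (simulated, 400,000 runs):

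| SD obese : control | Student | Welch |
|---|---|---|
| 1 : 1 | 81.7% | 79.8% |
| 1.25 : 1 | 67.1% | 78.1% |
| 1.5 : 1 | 49.9% | 75.8% |
| 2 : 1 | 20.7% | 70.7% |

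At equal SDs, Welch's loss is about 1 to 2 points for differences of 0.3 to 0.7 SD.

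**Balanced comparisons.** At 300 versus 300 (study group 1 against 2) and 330 versus 330 (no GDM against GDM), Student's simulated level is 4.9 to 5.1% for SD ratios from 1/3 to 3.

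**HC3 in the two-group case.** Its squared standard error is s₁²/299 + s₂²/29, against s₁²/300 + s₂²/30 for Welch. With unit variances this is 0.0378 against 0.0367. HC3 therefore carries nearly the same correction into a regression model.

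**The case against.** The strongest reply is about scope. The t test is assigned to descriptive baseline analysis only; outcomes go to regression and prediction to logistic models. A reader might infer that the comparison for which the controls are recruited, the biomarker panel at birth, will be tested by Student's t and will therefore have wrong p-values. The Protocol nowhere says so, and its Variables section lists cord-blood metabolites as exposures rather than baseline characteristics. This part of the objection stands.

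It does not remove the point. Maternal obesity is a listed exposure and univariable linear regression is planned, so the same pooled arithmetic can reach birth weight and C-peptide at 10:1. The Protocol fixes no standard-error method for those models. That is ordinary analysis-plan detail, so HC3 is a recommendation here and its absence is no fault.

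A second reply is that pooling is not stated and that R's own t-test function defaults to Welch. That is true, but Student's t conventionally means the pooled test. The named test and the software default thus point different ways, which is a reason to settle the wording.

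Third, all sizes rest on assumed SDs. A reader might infer from the BMI limits that the obese group will be more variable throughout and that real differences will most likely be missed. The limits show this only for maternal BMI, where the groups differ by design and a p-value hardly matters. For birth weight, C-peptide or HbA1c it is plausible but not shown, and the direction could be the reverse.

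Finally, with 30 controls an expected count falls below 5 whenever the overall prevalence is under 5/30 = 16.7%. Switching to Fisher's exact test in that case is routine detail and no fault of the Protocol.

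**Conclusion.** The point holds as a minor improvement to a stated method. At 300 versus 30, pooled-variance inference has a true level of about 1.9% or 10% when the SDs differ by a factor of 1.25, and about 0.1% or 25% at a factor of 2, depending on which group is more variable. Welch's test holds 5% throughout.

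This rests on reading Student's t in its usual pooled sense, on normal data, and on SD ratios that the Protocol does not supply. If the SDs are equal, nothing is wrong with the level. The point concerns only obese versus normal-weight contrasts: the descriptive ones, and linear models that carry that contrast. The study's main aim, predicting childhood obesity risk from biomarkers, does not rest on it.

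**What to change.** In the Statistical analysis section, name Welch's t test for comparisons of obese with normal-weight women. For linear models that contain this contrast, specify heteroscedasticity-robust (HC3) standard errors, here or in the analysis plan. No sample size, visit or data collection changes.

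The cost is one line of wording and, for Welch's test, about 1 to 2 points of power if the SDs turn out equal (for example 79.8% instead of 81.7% at a difference of 0.55 SD). The change is therefore cheap but not entirely free.

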**Sources of funding**

The study is supported by the German Federal Ministry of Education and Research grant 01EA1307 to [name] and the Foundation for Cardiovascular Prevention in Childhood, Ludwig-Maximilians-Universität München, Munich, Germany.

